### *Randomization*

Randomization will take place at the end of the study measurement visit within the first week postpartum. Randomization will follow a dynamic permuted block design. Randomization numbers will be generated prior to the start of the study, and placed in sequentially numbered opaque envelopes. Randomization envelopes will be stored in a locked cabinet in the study office at UCT that will be accessed by the study coordinator when a woman is fully consented and has completed the immediate postpartum study visit, with independent documentation of the participant ID number, randomization date, and randomization assignment. The study coordinator will provide the MOU-ART service with a regularly updated list of women to be retained within the MOU-ART service until they have ended breastfeeding. The study coordinator involved in randomization will not be involved in interviewing participants.

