### ***Six week postpartum study visit (study visit 5)***

Mother-infant pairs in both trial arms will be seen at 6-8 weeks postpartum. At this visit (lasting 30-45 minutes):

- Questionnaires will be administered on recent maternal, child and HIV-related health care, HIV disclosure, and ART use (including side effects and adherence). Additional instruments will collect data on HIV treatment knowledge, beliefs about ART medications, stigmatization, and mental health measures (including psychological distress, and perinatal mood), infant feeding practices, and infant health and health care (including adherence to daily nevirapine prophylaxis).
- Mothers will undergo phlebotomy to draw 5mL of venous blood for storage and batched viral load testing.
- Mothers height, weight and mid-upper arm circumference will be measured
- Growth parameters of the infant will be measured (weight, length, head circumference and mid-upper arm circumference)

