***Twelve month postpartum visit (study visit 9)***

Mother-infant pairs in both trial arms will be seen at 12 months postpartum. At this visit (lasting 60 minutes):

- Questionnaires will be administered on recent maternal, child and HIV-related health care, HIV disclosure, ART use (including side effects and adherence) and quality of life. Additional instruments will collect data on quality of HIV care, maternal family planning, partner violence, future pregnancy intentions, and mental health measures (including alcohol/substance abuse), infant feeding practices, food security and infant health and health care

- Mothers will undergo phlebotomy to draw 5mL of venous blood for storage and batched viral load testing.
- Mothers weight and mid-upper arm circumference will be measured
- Growth parameters of the infant will be measured ( weight, length, head circumference and mid-upper arm circumference)
- Infants will undergo phlebotomy. No more than 5mL of venous blood will be drawn for HIV PCR testing with storage of remaining specimen. Results of this HIV testing will be returned to mothers by study staff, with urgent recall of any infant found to be infected for referral to clinical care. This blood will also be used to conduct a rapid antibody test for research purposes.
- After completion of above study procedures, mothers pairs will be invited to participate in an additional infant neurodevelopmental assessment. Infants will be screened for eligibility based on the criteria outlined in Section 4. If eligible, mothers will complete a separate written informed consent form. Those who consent to the additional assessment will be given the option to complete the neurodevelopmental assessment immediately (on the same day as 12 months postpartum visit) or be scheduled for an additional visit to take place within 4 weeks from the 1 year birthday of your baby.

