### **Abstraction of routinely collected clinical information**

In addition to the study measures described above, chart reviews will be conducted in order to collect key data on participants regarding (a) antenatal and obstetric care and (b) ART initiation and follow-up. Permission to review clinical records of participants is included in informed consent documents for all participants.

- *Antenatal information* will be taken from MOU records, including the results of routine bloods (syphilis screening, ABO blood group), the number and timing of ANC visits, the results of prenatal ultrasound scan, and any evidence of antenatal complications including episodes requiring referral to specialist obstetric care.
- *PMTCT information*. Will come from antenatal and obstetric records, including: CD4 enumeration, dates and types of antiretroviral drugs received.
- *Obstetric information* will be abstracted from the records at the MOU or nearby obstetric hospitals. We will abstract the date and time of the onset of labour and rupture of membranes, the progress of labour and evidence of fetal distress, the date, time and mode of delivery; birth outcome; any PMTCT interventions received; Apgar scores at 1 and 5 minutes postpartum; neonate mass, head circumference and length, and placental weight.
- *ART initiation and follow-up data* will be abstracted at the end of the study from routine clinical care records maintained by the general ART and MOU-ART services. Items to be abstracted from these clinical records include: date of initial presentation to the ART service; pre-ART clinical history, examination and laboratory investigations (including TB-related history and WHO staging); date of ART initiation; dates of routine follow-up visits post-ART initiation and major clinical events, including clinical findings that may suggest opportunistic infections, ART side effects, drug toxicities; pharmacy dispensing & refill information; and missed follow-up visits and retention in care. Information through 18 months postpartum will be abstracted on all participants from the relevant clinical records at either the general ART or the MOU-ART service, as appropriate.

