| Infant growth and well-being                    |                                                    |                                                          |                                                   | X                                                     | X                                                                  | X                               | X                               | X                               | X                                | X                                 |
| Infant HIV PCR result               |                                                    |                                                          |                                                   |                                                       | X                                                                  |                                 | X                               |                                 |                                  |                                   |

1. Participants' locator information will be updated at each study visit, if it has changed since the last visit.
2. These assessments will be administered to participants who are already on ART at the time of enrolment into Phase 1.
3. A subset of demographic questions will be asked at all antenatal and postnatal study visits.
4. Kessler-10 (screening questionnaire for non-specific psychological distress) and Edinburgh Postnatal Depression Survey.
5. Alcohol use disorders identification test (AUDIT) and drug use disorders identification test (DUDIT).
6. Adherence assessments will include maternal ART adherence and, postpartum, questions related to infant adherence nevirapine prophylaxis and co-trimoxazole.
7. Note that maternal weight & mid-upper arm circumference will be measured at each Phase 3 study visit; maternal height will only be measured at the 6 week postpartum visit
8. Abstraction of routine clinical data and laboratory data will take place at the end of the study.
9. Results of routine laboratory testing on mothers (including pre-ART and on-ART CD4 cell count, pre-ART serum creatinine, alanine aminotransferase and full blood count) and infants (HIV PCR at 6 weeks and 2 weeks after cessation of breastfeeding; here marked for the 6 month visit) will come from record review.
10. 10. PCR testing will only be conducted on infants who are positive per rapid antibody test

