Secondary objective 2.4 will be addressed through analyses of the association between demographic, psychosocial and clinical measures (including characteristics of antenatal ART use) on the primary outcome. Analyses will parallel the pure count and time-to-event methods described for the primary objective. In addition, we will use proportional hazards models to identify measures independently associated with the primary outcome and its constituents; variable selection will be based on directed acyclic graphs developed *a priori* to help distinguish causal intermediates from confounding variables (for instance, antenatal ART adherence may be a causal intermediate through which demographic or psychosocial characteristics influence the primary outcome, rather than a confounder). All regression analyses will include trial arm as a covariate; other aspects of model building and diagnostics will follow standard approaches. Outputs will be expressed as hazard ratios and 95% confidence intervals.

Comparison of secondary outcomes between the two postnatal ART services will employ both pure count and person-time methods, as described above. Patterns of women's missed visits during the postpartum period (objective 2.5.A) will be analysed according to the frequency of different numbers of missed/late visits, and the timing of the missed/late visits during the postpartum. Breastfeeding practices (objective 2.5.B) will be analysed according to the duration of exclusive breastfeeding from birth; the duration of mixed feeding; and the timing of final infant exposure to breastmilk. Maternal viral suppression (objective 2.5.C) will be analysed according to the frequency and timing of detectable viraemia (with cutpoints at <50 and <1000 copies/mL) as well as 'survival' to detectable viraemia through 12 months. Incidence of infant respiratory and/or diarrhoeal illness (objective 2.5.D) will be analysed using person-time methods; comparisons of infant growth parameters will use dependent (intra-child) and independent (between child) comparisons. Rates of mother-to-child transmission will be compared at 6 weeks and 12 months using pure count methods (objective 2.5.E).

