The BSID-III developmental scores by subscale, using raw, composite and percentile scores, will address objective 2.6. Developmental delay will be classified as more than 1 standard deviation from mean. Although the BSID-III normative scores are based on United States-based populations, similar scores were observed in a South African population, in a similar setting to ours. Based on consultation with paediatric developmental specialists in our area, a difference in mean score of >5 will be used to define a clinically significant difference between subgroups. The primary exposure variable will be maternal HIV disease severity during pregnancy, as measured by clinical, immunological and virological measures at booking and delivery. Third variables will be identified *a priori* via directed acyclic graphs; these will include baseline, cumulative and time-varying measures (including maternal mental health, antenatal alcohol

and/or substance abuse, food insecurity, household asset index, gestational age, birth weight and subsequent infant growth). Throughout, units of analysis will be mother-infant pairs, with maternal and infant exposures as predictors of infant neurodevelopment. The distributional attributes of the BSID-III scores will determine the final generalized linear models of choice. A mixed effects model will be utilized to allow for repeated exposure measures and missing data.

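### The infant growth comparison names no adjustment for birth size, although birth weight, length and head circumference are collected and predate randomisation; adding it is a cheap, modest gain in precision.

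*Protocol*

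**What the plan says.** Objective 2.5.d of the protocol promises a comparison of infant growth between the two services. The method stands in section 10, Data analysis: "comparisons of infant growth parameters will use dependent (intra-child) and independent (between child) comparisons". No test, model, scale, time point or covariate follows. The general rule at the start of that paragraph, "Comparison of secondary outcomes between the two postnatal ART services will employ both pure count and person-time methods, as described above", is meant for events and person-time and does not suit a continuous measurement. The growth clause is therefore the only growth method in the document.

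Three other places bear on the point:

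- **Birth size.** Under Abstraction of routinely collected clinical information, the obstetric items include "neonate mass, head circumference and length, and placental weight".
- **Follow-up size.** From the six-week visit to the 18-month visit the study measures each infant's "weight, length, head circumference and mid-upper arm circumference".
- **Randomisation.** "Randomization will take place at the end of the study measurement visit within the first week postpartum".

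In the next part of Data analysis, the neurodevelopment (BSID-III) analysis lists "gestational age, birth weight and subsequent infant growth" among its third variables and names a mixed effects model. Neither appears for growth.

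**The concern.** Birth size is a child's own starting value for the outcome. It is already being collected, and the allocated service cannot have influenced it. A between-arm comparison of later size that leaves it out carries variation that could have been removed. It also leaves any chance imbalance in birth size inside the estimated arm difference.

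The study's own growth measurements cannot serve as a clean baseline. They begin at 6-8 weeks, after randomisation and within the window in which Arm A women are referred. The birth values are the infant size measurements that are certain to precede allocation.

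The protocol names birth weight as a variable for neurodevelopment but not for growth, where it is the baseline of the outcome itself. At stake is precision on one part of a secondary objective, and the clarity of having one named model for the arm difference.

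**Working it through.** **Is there a figure to reproduce?** No. The protocol gives no standard deviation, correlation, target difference or power for growth. Its sample size table concerns the primary endpoint only and is not affected.

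**Is birth size a valid baseline?** The values date from birth. Randomisation comes at the end of the first postpartum visit, within a week, with an allowable window to 28 days in the Phase 3 inclusion criteria. The schedule notes say that "Abstraction of routine clinical data and laboratory data will take place at the end of the study", but late abstraction does not change when the value was generated. Weight, length and head circumference therefore have a pre-randomisation value. Mid-upper arm circumference has none listed.

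**How much precision is at stake?** Let r be the correlation between birth size and size at a later visit, with equal standard deviations on a standardised scale. Take the variance of the arm difference from a comparison that ignores birth size as 1.

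- Birth value as covariate: 1 - r².
- Change from birth, if that were used: 2(1 - r).
- Ratio of the first to the second: (1 - r²) / [2(1 - r)] = (1 + r)/2.

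The covariate form is below 1 for any non-zero r, and below the change form for any r under 1. The direction therefore does not depend on the assumed correlation; only the size does.

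To put the gain on a clinical scale, take 195 women per arm less the originally expected 20% loss: 195 × 0.80 = 156 infants per arm, assuming one infant per woman. The difference detectable with 90% power at two-sided 0.05, ignoring birth size, is (1.960 + 1.282) × √(2/156) = 0.367 SD. With the covariate, multiply by √(1 - r²).

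| Assumed r | Variance with birth covariate | Fall in standard error | Detectable difference (SD) | Variance of change from birth |
|---|---|---|---|---|
| 0.2 | 0.96 | 2.0% | 0.360 | 1.60 |
| 0.3 | 0.91 | 4.6% | 0.350 | 1.40 |
| 0.4 | 0.84 | 8.3% | 0.336 | 1.20 |
| 0.5 | 0.75 | 13.4% | 0.318 | 1.00 |

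The figures are for a single visit. The correlation may differ between visits and between parameters. The 156 is an illustration, since the protocol says that loss is running above 20% and gives no new rate.

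**The case against.** The strongest reply is that the clause is a one-line outline. It names no covariate but excludes none, and covariates for a secondary outcome are ordinary matter for a statistical analysis plan, which is not shown. A repeated-measures model with arm and arm-by-visit terms draws on both within-child and between-child information, so the proposed model could be seen as filling in the clause rather than correcting it.

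Much of that stands, and it rules out some stronger readings:

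- A reader might infer that the protocol commits to an unadjusted test. It does not use that word, and the inference goes beyond the text.
- A reader might take the within-child comparison to mean change from birth, and charge the plan with the larger variance in the last column. The clause does not tie the within-child comparison to birth. It could equally mean change across the six study visits.
- A reader might want 12 months fixed as the single reported growth estimate. Objective 2.5.d names no time point and growth is measured to 18 months, so that is a preference.
- A reader might call the gain free. Birth values come from routine records at the midwife unit or nearby hospitals, and the protocol gives no completeness figure.

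What the reply does not remove is that this protocol names models and covariates where it intends them: regression with trial arm as a covariate for objective 2.4, and a mixed model with birth weight among the third variables for neurodevelopment. For growth it states two kinds of comparison, and a better method using data already collected is available.

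**Conclusion.** The point holds as a minor improvement in efficiency. The protocol names only within-child and between-child comparisons for growth and no adjustment for birth size, while valid pre-randomisation values exist for three of the four parameters. Using them lowers the standard error by about 2% to 13% against a comparison that ignores birth size. That range rests on assumed correlations of 0.2 to 0.5 and equal standard deviations, neither of which the protocol gives. At the low end the gain is negligible; at the high end it is useful.

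A reader might go further and infer that the growth results would be biased. They would not be: under randomisation, leaving out a baseline covariate costs precision, not validity.

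**What to change.** Replace the growth clause in Data analysis, or settle it in the statistical analysis plan before outcomes are unblinded, with wording such as:

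*Infant weight, length and head circumference, on an age- and sex-standardised scale, will be compared between arms in a repeated-measures linear model with arm, visit, arm-by-visit interaction and the birth value of the same parameter as covariate. For mid-upper arm circumference the covariate will be birth weight. Missing birth values will be handled by simple imputation of the baseline covariate.*

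The arm-by-visit term gives an arm difference at each visit; the trial team can name a lead visit if it wants one. The cost is analysis wording only, with no new data, visits or procedures. The one small downside is missing birth records. Their number should be reported by arm.

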### **Secondary objectives**

- 2.1 To characterize the health status of the population of HIV+ pregnant women seeking antenatal care at the Gugulethu Midwife Obstetric Unit (MOU) including maternal and infant outcomes
- 2.2 To describe uptake and timing of services received throughout the PMTCT cascade, including antenatal ART initiation and follow-up, at the Gugulethu MOU
- 2.3 To examine whether there is variation in the impact of the two postpartum HIV care strategies on the primary outcome between subgroups of women according to their demographic, clinical and psychosocial characteristics, measured antenatally and postnatally.
- 2.4 To describe changes in women's clinical and/or psychosocial characteristics between the antenatal and postnatal periods, and investigate how these are independently associated with the primary outcome
- 2.5 To compare MCH-focused ART services to general adult ART services on:
  - a. Women's missed visits and loss to follow-up on ART up to 18 months postpartum
  - b. Breastfeeding practices, including duration of exclusive feeding and weaning patterns
  - c. Maternal viral suppression throughout the breastfeeding period as well as before and after cessation of breastfeeding
  - d. Infant health outcomes including growth parameters and incidence of respiratory and/or diarrhoeal illness
  - e. Rates of HIV transmission from mother-to-child at 6 weeks and 12 months postpartum
  - f. Acceptability of different strategies for delivering HIV care and treatment during the postpartum period
  - g. Cost-effectiveness in delivering HIV care and treatment during the postpartum period
  - h. Developmental scores of 1 year old infants

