#### General adult ART management strategy

Women and infants randomized to the general adult ART management strategy will receive postpartum ART services according to the local standard of care. Specifically, women will be referred from the MOU ART service to their nearest adult ART clinic at their first postpartum ART clinic visit, at around 6 weeks postpartum. The precise timing of this referral will depend on the scheduling of women's ART visits, and may take place between approximately 4 and 8 weeks after birth. Infants will be referred for routine infant care to local primary care clinics, following standard of care in this setting.

The specific facility women are referred to will be determined by their area of residence. For women who reside within Gugulethu itself, referral will be to the ART service at the Gugulethu CHC (located approximately 100 metres from the MOU; this applies to approximately 60-70% of women attending the MOU); the corresponding infant referral is to one of four primary care clinics in the local community. For women who live in other communities (with the Gugulethu MOU as their closest antenatal clinic, but not their closest ART clinic), referral will be to their nearest adult ART clinic, primarily facilities serving the communities of Philippi and Nyanga. All infants will be referred to their nearest routine infant follow-up service. Women may be referred to other facilities (e.g., in other parts of Cape Town or in the Eastern Cape) upon request.

In addition, midwives working in the MOU-ART service may opt to refer a woman to a higher level of medical care (e.g., if there is concern regarding ART toxicity) or on the basis of clinical or psychosocial grounds (if there are concerns regarding non-adherence). Reasons for deferred or alternate referral are documented in the clinical record.

On the day of referral, all women receive counselling on long-term ART adherence, the ongoing risks of MTCT through breastfeeding, and the need for repeat infant HIV testing. Following provincial protocols, referrals employ a Western Cape ART transfer form, completed in duplicate. The original form is sent with the patient, and the copy is retained in the patient's MOU folder. Patients are prescribed one month of treatment and advised to make an appointment at their referral clinic as soon as possible before their one-month ART supply is finished.

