***Eighteen month postpartum visit (study visit 11)***

Mother-infant pairs in both trial arms will be seen at 18 months postpartum. At this visit (lasting 60 minutes):

- Questionnaires will be administered on recent maternal, child and HIV-related health care, HIV disclosure and ART use (including side effects and adherence). Additional instruments will collect data on maternal family planning, future pregnancy intentions, and mental health measures, infant feeding practices, and infant health and health care.

- Mothers will undergo phlebotomy to draw 5mL of venous blood for storage and batched viral load testing.
- Mothers weight and mid-upper arm circumference will be measured
- Growth parameters of the infant will be measured ( weight, length, head circumference and mid-upper arm circumference)
- Infants who are not known to be HIV-infected will undergo phlebotomy. No more than 5mL of venous blood will be drawn and used to conduct a rapid antibody test. For those infants who are reactive via antibody test, additional HIV PCR testing will be conducted with storage of remaining specimen. Results of this HIV testing will be returned to mothers by study staff, with urgent recall of any infant found to be infected for referral to clinical care.

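### Infant development is a between-arm objective (2.5.h), but BSID-III is analysed by maternal HIV severity under an unlisted objective 2.6; the delay rule has no direction, and 6-week transmission is close to a baseline measure

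*Protocol*

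**What the plan says.** In the Protocol, Secondary objectives, item 2.5 opens with "To compare MCH-focused ART services to general adult ART services on" and then lists its outcomes. Item e is mother-to-child transmission at 6 weeks and at 12 months. Item h is "Developmental scores of 1 year old infants".

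Under Data analysis, the BSID-III paragraph assigns the scores to objective 2.6. It states "The primary exposure variable will be maternal HIV disease severity during pregnancy", sets a mean difference above 5 points between subgroups as clinically significant, and adds "Developmental delay will be classified as more than 1 standard deviation from mean". Trial arm is not mentioned in that paragraph.

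For transmission, Data analysis says "Rates of mother-to-child transmission will be compared at 6 weeks and 12 months using pure count methods". The section on the general adult ART management strategy has Arm A mothers referred "at their first postpartum ART clinic visit, at around 6 weeks postpartum", with an allowed range of about 4 to 8 weeks. Under Infant follow-up, the early infant PCR is done at 6 weeks.

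**The concern.** The objective and its analysis do not match. A reader of the objectives expects developmental scores to be compared between randomised arms. A reader of the analysis text gets an observational study of maternal disease severity, attached to an objective number that leads nowhere. If the text is followed, a stated trial objective goes unreported. If an arm comparison is added later, it will look unplanned.

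The delay rule, read literally, counts infants who score well above the mean as delayed.

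The 6-week transmission comparison is set beside the 12-month one as though both tested the strategies. At 6 weeks the mothers' ART care has barely begun to differ, so a null result would say nothing about the strategies, and a chance difference could be taken for an effect.

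**Working it through.** **BSID-III: the texts side by side**

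| Place in Protocol | What it fixes |
|---|---|
| Secondary objectives, 2.5.h | Developmental scores at one year, compared between the two services |
| Study design, Phase 3 | Cites an objective 2.6 |
| Data analysis, BSID-III | Cites objective 2.6; exposure is maternal severity; 5-point difference judged between subgroups |
| Secondary objectives, whole list | Ends at 2.5.h; there is no 2.6 |

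Two sentences elsewhere in Data analysis might fill the gap, and neither does. One puts trial arm into every regression as a covariate, but it stands in the paragraph on objective 2.4, among proportional hazards models reported as hazard ratios. Even if it reached BSID-III, arm would be an adjuster and not the contrast of interest. The other gives count and person-time methods for comparing secondary outcomes between the services. Neither method suits a continuous score.

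**Is the arm comparison worth making?** The plan's main sample size is 292 in total for 25% against 10%, 90% power, two-sided 0.05. It reproduces with the continuity-corrected two-proportion formula: 146 per arm, 292 in total. I use 146 per arm as an illustrative number of assessed infants. For a 5-point difference:

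- n per arm = 2 × (SD/5)² × (z for alpha + z for power)². The SD is an assumption. With SD 15 and 80% power: 2 × 9 × (1.960 + 0.842)² = 141.3, so 142 per arm. For 90% power it is 190.
- Power with 146 per arm: SD 15 gives 81%; SD 12 gives 95%.

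**Delay rule, assuming normal scores**

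- More than 1 SD below the mean: P(Z < −1) = 0.159.
- More than 1 SD in either direction: P(|Z| > 1) = 0.317, half of them high scorers.

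**6-week transmission**

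- Randomisation is in the first week postpartum, with eligibility allowed up to 28 days, so in-utero and intrapartum exposure come before it.
- Arm A referral is at about 6 weeks (4 to 8), with one month of treatment in hand. The infant PCR is at 6 weeks. Almost all the exposure that this test can reflect therefore precedes a difference in maternal ART care.
- Under Setting, the 6-week rate at the site is 2–4%. With 195 per arm: 0.02 × 195 = 3.9 and 0.04 × 195 = 7.8 infections per arm.
- Power of Fisher's exact test for a true 4% against 2%: 13% with 195 per arm, 8% with 146, 17% with 240.

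**12-month transmission.** Let b be the shared early risk and r the later risk in Arm A, and suppose that Arm B halves r. The cumulative risks are b + (1 − b)r and b + (1 − b)r/2. The values of r are assumptions.

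| b | r | Arm A | Arm B | Risk ratio |
|---|---|---|---|---|
| 0 | 1% or 2% | r | r/2 | 0.50 |
| 2% | 1% | 2.98% | 2.49% | 0.84 |
| 2% | 2% | 3.96% | 2.98% | 0.75 |
| 4% | 1% | 4.96% | 4.48% | 0.90 |
| 4% | 2% | 5.92% | 4.96% | 0.84 |

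The risk difference hardly moves. With r = 2% it is (1 − b) × 1%, which is 1.00, 0.98 and 0.96 percentage points for b = 0, 2% and 4%.

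**The case against.** The best defence on BSID-III is that the two references to 2.6 show a separate observational objective that was misfiled as 2.5.h, so no arm analysis was ever intended. That may be how the text arose, but it does not rescue it. As it stands, the list makes development a between-arm outcome and the analysis does not, so one of them must change. It is also fair to say that an arm comparison here is not a clean randomised one. Section 4 limits the assessment to infants of women who completed 12 months, with no known infant HIV infection and no major anomaly.

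On delay, the word itself implies the lower tail, so the rule is incomplete more than wrong. That stands, and one word settles it.

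On transmission, a reader might infer that objective 2.5.e cannot be answered at all. The documents do not support that. The quoted sentence also covers 12 months, well after referral. Early infections are balanced in expectation by randomisation; they dilute the risk ratio but leave the risk difference almost unchanged. Nor is the 6-week comparison wholly empty, since some Arm A mothers leave from 4 weeks and the infant's care site may already differ. Restricting the comparison to infants without a positive 6-week PCR has its own weakness: that test is routine, taken from records, and done at sites that may differ by arm.

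Three further readings are tempting but unsupported:

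- That the 18-month test ("Infants who are not known to be HIV-infected will undergo phlebotomy") obliges a comparison at that time. Objective 2.5.e names 6 weeks and 12 months, and the Background expects the vast majority of breastfeeding women to stop by 6 months.
- That "A mixed effects model will be utilized to allow for repeated exposure measures and missing data" specifies a model that cannot be identified. The text names no child random intercept on a single score and leaves the final model to the score distributions.
- That early infections would be most of the events. The Background says transmission after 6 weeks is poorly understood.

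**Conclusion.** The point holds mainly for BSID-III. Objective 2.5.h is a between-arm comparison with no between-arm analysis, and the analysis given serves an objective that is not listed. This follows from the text alone and needs no numerical assumption. The missing comparison would be informative: about 81% power for 5 points with 146 infants per arm if the SD is 15, and 95% if it is 12. Both SDs and the number assessed are assumptions.

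Two lesser points also hold. The delay rule needs a direction; on normal scores the literal reading doubles the share flagged, from 15.9% to 31.7%. The 6-week transmission comparison is close to a baseline comparison and should not be read as a test of the strategies. The 12-month comparison is sound, though its risk ratio is diluted (0.50 becomes 0.75 to 0.90 under the assumptions above) and events will be few. The 3.9 to 7.8 early infections per arm rest on the site's general 2–4% rate, which may not apply to breastfeeding women on ART. These are secondary objectives, so the changes are advisable but do not touch the primary analysis.

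**What to change.** 1. For 2.5.h, add a comparison of mean BSID-III scores by randomised arm. State that assessed infants are a subset selected after randomisation, and report by arm how many were eligible and assessed.
2. List the maternal-severity analysis as a separate observational objective, and correct the references to 2.6 in Study design and Data analysis.
3. Define delay as more than 1 SD below the mean.
4. Report 6-week transmission by arm as a near-baseline description, without treating it as a test of the strategies.
5. Keep the 12-month comparison by arm. As support, report infections first detected after 6 weeks, with a stated rule for infants who have no 6-week PCR result.

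The cost is revised wording and a little more analysis, with no new visits or tests. The supportive transmission analysis will have few events and depends on how complete the routine 6-week results are in each arm.
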